### Outcome definitions {26}

*Primary outcome*. The quality of sputum samples, binary outcome*Secondary outcome 1*. Number of adverse events, discrete outcome
Aggravation of SaO_2_ and SaO_2_ ≤ 93% (COPD patients ≤ 88%), binaryAggravation of RR and RR lower than 12 or higher than 20 times per minute, binaryOccurrence or aggravation of symptoms (cough, expectoration, dyspnea, chest pain), binaryAggravation of patient symptoms experience, binaryOccurrence of side effects observed by the project assistant, binaryDeath within 7 days from admission, binary30 days re-admission after current hospitalization, binary*Secondary outcome 2*. Patient experience of the sputum collection procedure, ordinal outcome

### Harms {30}

The project includes collecting methods that are already applied and recommended in clinical practice. There are minimal indications of adverse effects of a spontaneous cough or induced sputum after inhaling an isotonic saline solution (0.9%) [21, 22]. It is known that the tracheal suction routine carries a risk of airway bleeding, although this is rare and often short-lived [20]. Moreover, there may be short-term discomfort, especially during the tracheal suction procedure [19]. Patients will be informed of the adverse events verbally and in writing. In case of an aggravation of symptoms, the procedure that is being performed will be interrupted preventing patient participation. The procedures are known to have minimal risks and the hospital will provide routine ancillary post-trial care, if necessary.

### Data management {32}

Data management plan version 1.0 is attached to the Additional file 4.

### Data monitoring

During the data collection, an extern assessor will supervise the performance of all project assistants and an independent microbiologist expert will ensure data quality and continue registration of the specimens. The daily inclusion of participants will be monitored by the project investigator and discussed with the study assistants and steering committee.

After primary analysis of data, the results will be discussed and evaluated first in the steering committee and afterwards with all involved hospital departments.

## Statistical method

### Sample size consideration {11}

It is hypothesized that the intervention group receiving expiratory techniques is non-inferior to the tracheal suction group. Grouping two methods in the intervention arm, there will be fewer missing values and only two comparison groups.

Based on clinical practice and literature, it is assumed that no sample will be obtained from 50% of patients by forced expiratory technique alone [9, 10, 42], 30% from patients by sputum induction combined with the forced expiratory technique [23, 43], and 10% from patients using tracheal suction [28]. The proportion of obtained samples classified as good quality is assumed to be 75% for the procedures using expiratory techniques [23, 27, 43] and 90% for tracheal suction [28].

Considering these assumptions, the study’s power is 84% with 260 patients, including missing values. The power of the study was calculated with a Monte Carlo simulation using logistic regression.

An internal register showed that at least 1250 patients were admitted to the study ED with suspicion of infection annually, and of these, 600 patients were diagnosed with pneumonia. Including 260 patients with suspected LRTI will take five months, taking into account exclusion criteria, weekends/holidays, and missing data.

To avoid overfitting in the primary analysis, we followed the relaxed one in ten rule for the fixed effects and one in 20 rule for the random effects [44].

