**Method:**

The design is a pragmatic, non-inferiority, parallel-arm randomized controlled trial including 280 patients admitted with suspected lower respiratory infection to two emergency departments. Patients are randomized to a usual care group, where sputum samples are collected by tracheal suction or to an intervention group where sputum samples are collected by forced expiratory technique and sputum induction. The statistical analysis will follow an intention-to-treat protocol. This SAP is developed and submitted before the end of recruitment, database closure, and statistical analyses.

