## Adherence and protocol deviations {19}

### Adjustments after the study start and before recruitment completion

Due to the SARS-CoV-2 pandemic, patient distribution was altered, and it was necessary to extend the recruitment to include the second site. The study period was adjusted with study start from October 19th to November 9th, and study completion from March 1st to July 5th and will include at least 260 participants. New sample size and power calculations were performed where the clinical significant absolute difference was set at 15% points. The personnel conducting the sample size calculations do not know the participants’ outcomes.

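### The stated 84% power belongs to a test of a 90% versus 75% difference, not to the non-inferiority hypothesis that it is offered to support

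*SAP article*

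**What the plan says.** The section Sample size consideration {11} begins: "It is hypothesized that the intervention group receiving expiratory techniques is non-inferior to the tracheal suction group". It assumes that no sample is obtained from 50% of patients by forced expiratory technique alone, from 30% by induction combined with that technique, and from 10% by tracheal suction. Good quality among obtained samples is "assumed to be 75% for the procedures using expiratory techniques" and 90% for suction. On these assumptions it reports that the study's "power is 84% with 260 patients, including missing values", a figure "calculated with a Monte Carlo simulation using logistic regression".

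The section on adjustments after the study start says that power was recalculated and that "the clinical significant absolute difference was set at 15% points". It adds that the trial "will include at least 260 participants". The Abstract describes a "parallel-arm randomized controlled trial including 280 patients".

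The article nowhere calls any figure a non-inferiority margin. It sets significance at p < 0.05 without stating sidedness, and it plans 95% confidence intervals.

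**The concern.** In a non-inferiority design, power is the chance that the confidence limit for the treatment difference clears the margin, given an assumed true difference. Here the assumed true difference is unfavourable to the intervention and equals the plan's own clinically significant difference. A calculation that gives high power under that assumption is measuring the chance of showing that expiratory techniques are worse, which is the opposite of the hypothesis in the section's first sentence.

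A reader will take 84% as the chance of confirming non-inferiority. The planned primary result is an odds ratio with a p-value, so a non-significant result might then be read as non-inferiority from a trial believed to be adequately powered for it.

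**Working it through.** **Inputs** (Sample size consideration {11}, unless noted): 260 patients; 1:1 allocation (Randomization {10}), so 130 per arm; good quality 0.90 (suction) and 0.75 (expiratory) among obtained samples; 10% uncollected with suction. Uncollected samples count as missing (Microscopy). Two readings of the intervention arm are possible:

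- 30% uncollected overall: 130 × 0.70 = 91 evaluable.
- 30% of the 50% who fail the first technique, that is 15%: 130 × 0.85 = 110.5 evaluable.

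The suction arm has 130 × 0.90 = 117. Two-sided alpha of 0.05 is assumed because 95% intervals are planned.

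**Step 1: reproduce the 84% as a test of difference.** Power = Φ[(0.15 − 1.96·SE₀)/SE₁], where SE₀ uses the pooled proportion and SE₁ the separate ones.

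- 117 vs 91: pooled p = (105.3 + 68.25)/208 = 0.834. SE₀ = √(0.834 × 0.166 × (1/117 + 1/91)) = 0.0520. SE₁ = √(0.09/117 + 0.1875/91) = 0.0532. Power = Φ(0.905) = 81.7%.
- 117 vs 110.5: SE₀ = 0.0502, SE₁ = 0.0497. Power = Φ(1.041) = 85.1%.

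Simulated logistic regression, the plan's own method, gives 82.0% (Wald) and 82.6% (likelihood ratio) with 30% uncollected, and 85.4% and 86.2% with 15%. The range of 82–86% brackets the stated 84%.

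**Step 2: non-inferiority power under the same rates.** With margin M on the risk difference, power = Φ[(M − 0.15)/SE₁ − z], with SE₁ = 0.0532 (117 vs 91) and z = 1.96 for one-sided 0.025.

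| Margin M | Argument of Φ | Power |
|---|---|---|
| 0.10 | −0.940 − 1.96 | 0.2% |
| 0.15 | 0 − 1.96 | 2.5% (simulated 3.1%) |
| 0.31 | 3.008 − 1.96 | 85% |

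At one-sided 0.05 and M = 0.15 the formula gives 5.0%; simulation gives 5.4–5.7% across the two readings. A margin of about 31 points would be needed to reach 84–85%, roughly twice the 15-point difference that the plan calls clinically significant.

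**Step 3: illustration if the two methods are truly equal.** This is not the plan's assumption. Simulation, 260 patients, 95% interval, 30% then 15% uncollected in the intervention arm. The odds-ratio margin is the one implied by the assumed rates: (0.75/0.25)/(0.90/0.10) = 3/9 = 0.333.

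| Common rate | Risk-difference margin of 15 points | Odds-ratio margin of 0.333 |
|---|---|---|
| 90% | 93–96% | 65–69% |
| 85% | 84–88% | 80–83% |
| 80% | 76–81% | 88–90% |
| 75% | 70–74% | 92–94% |

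The ordering reverses between scales, so non-inferiority power cannot be stated until the scale is fixed.

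**Step 4: sample size.** With 280 patients the closed-form difference test gives 84.4% (126 vs 98) or 87.6% (126 vs 119).

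All figures leave out the personnel and site random effects and the multiple imputation, because the article gives no variance components.

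**The case against.** The strongest reply is that the article declares no margin, so the 3% is not a property of the plan. It comes from borrowing the 15-point clinically significant difference, and once the margin equals the assumed deficit, power equals the error rate by construction. That is right, and the 3% must stay conditional. A reader might infer that the trial has only 3% power for its hypothesis. The documents do not support this: with another margin or another assumed true difference the figure changes greatly, as Steps 2 and 3 show. What survives is that no margin near the plan's own 15 points makes the 84% a non-inferiority power under the stated rates.

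It can also be said that the match in Step 1 is not exact, and that one-sided 0.05 with 50% uncollected gives 83–84% too. That stands as well, but it is another test of difference and leaves the conclusion unchanged.

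The full protocol may hold a margin and a proper calculation. The point is not that something was left out: the hypothesis, the rates and the power appear together in one section and do not fit each other.

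Lastly, the 280 in the Abstract might be read as leaving it open which size the 84% belongs to. It does not: the sample size section ties 84% to 260, and 280 is compatible with a minimum of 260. The 280 is merely unexplained.

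**Conclusion.** The point holds. The 84% is consistent with power to detect 90% versus 75% (82–86% recomputed) and does not belong to the non-inferiority hypothesis under which it is stated. Taking 15 points as the margin, which is an assumption, non-inferiority power at the plan's own rates is about 3% at one-sided 0.025 and 5–6% at 0.05, and less at smaller margins.

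It would go too far to conclude that the trial is too small. If the methods were truly equal at rates of 75–90%, power with 260 patients would be about 70–96% for a 15-point risk-difference margin and about 65–94% for an odds-ratio margin of 0.333. The defect is a power figure attached to the wrong hypothesis. The 260/280 discrepancy is a separate, minor matter of reconciliation.

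**What to change.** In Sample size consideration {11}:

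1. Relabel the 84% as power to detect a difference between 90% and 75% good quality, with the sidedness of the test.
2. Declare the non-inferiority margin with its justification, its scale (risk difference or odds ratio) and the one-sided alpha. If the full protocol already sets a margin, cite it here.
3. State which reading of the 50% and 30% uncollected figures was simulated.
4. Restate non-inferiority power with 260 patients under an explicit assumed true difference. The figures in Step 3 illustrate the range and should not be copied in, because they depend on the margin and scale that the authors choose and leave out random effects and imputation.

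As a minor edit, explain the 280 in the Abstract or align it with the 260 in the sample size and adjustments sections.

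The cost is a text revision and one rerun of the existing simulation. The reported power may look less favourable. No extra enrolment is needed.

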### Statistics principles

#### Statistical interim analyses and stopping guidance {13}

No interim analysis will be conducted.

#### Timing of final analyses {14+15}

The final analyses will be conducted within three months of completion of inclusion, estimated to be ultimo September 2021. All outcomes will be analyzed collectively.

#### Confidence interval and *p*-value {16+17+18}

For the main analysis and the supplementary analysis with non-ordinal outcomes, 95% confidence intervals will be reported. For the supplementary analysis of the secondary outcomes, bootstrapped confidence intervals will be calculated for ordinal outcomes to accommodate lack of fit. A *p*-value less than 0.05 will be considered statistically significant.

No adjusting for multiple testing will be utilized in any analyses, as we only have one primary outcome [45].

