### Hypothesis, aim, and objectives {8 +12}

We hypothesize that expiratory techniques (forced expiratory technique and sputum induction) are non-inferior to tracheal suction in obtaining sputum samples from the lower respiratory tract.

This study aims to investigate the effectiveness of expiratory techniques compared to tracheal suction on the quality of sputum samples collected from patients acutely hospitalized with suspected LRTI.

The following objectives will be explored:
Is the proportion of suitable (good quality) sputum samples different when comparing samples obtained by tracheal suction to samples obtained by expiratory techniques?Is the number of adverse events different when comparing tracheal suction to expiratory techniques?How do patients experience the two sputum sample collecting procedures?

This statistical analysis plan (SAP) will describe the statistical analysis to be executed on primary and secondary outcomes to increase study transparency, reproducibility, and validity. This SAP was developed after the study protocol was registered with the following organizations: Danish ethics committee; clinical trials; data protection agency and, before database closure, data review; and commencement of any statistical analyses.

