#### Definition of analyses population {20}

The primary analysis will be conducted according to the intention-to-treat (ITT) principle [46, 47].

We define the ITT population as all admitted patients suspected of LRTI who sign informed consent and subsequently are allocate to one of two sputum collection groups. Sputum samples obtained by tracheal suction from patients in the intervention group, who are not able to expectorate, will be analyzed separately from the ITT analyses.

The primary analysis compares the tracheal suction group and the expiratory technique group to identify the most effective method for obtaining good quality sputum samples. The secondary analysis consists of an agreement analysis [48] between forced expiratory technique alone and forced expiratory technique after sputum induction.

Additionally, analysis of the secondary outcome of adverse effects will be conducted at baseline (right after allocation) and at the latest, 10 min. after the intervention. Clinical symptoms (cough, expectoration, chest pain, or dyspnea), SaO_2_, RR, and CR10 Borg scale [40] will be measured. Furthermore, a 5-point Likert scale will be used to measure patient experience of the procedure. The analyses will be adjusted for variables with a large influence on the outcome, which is an odds ratio larger than 2, to accommodate bias [49].

Descriptive analyses will be performed on the pathogens found when the specimens are cultured according to differential quality criteria.

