#### Analysis for primary outcome

For the primary outcome, the following analyses will be utilized:
To assess the suitability of the sputum sample between the two collecting methods groups, a hierarchical mixed effect logistic model with and without imputed values will be utilized to accommodate the random effect’s hierarchical structure, which manifests according to different personnel collecting the samples and geographical variation (Table 2).

**Table 2 Tab2:** Results of the primary outcome regarding specimens’ suitability and secondary outcome of adverse effects and patient experience. Tracheal suction method (reference group) compared to expiratory technique methods

Outcome	Unadjusted OR (CI) ***P***	Adjusted OR (CI) ***P***

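### The SAP declares a non-inferiority trial but states no margin and no rule for the confidence limit; its planning and analysis are for a difference

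*SAP article*

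**What the plan says.** The abstract states: "The design is a pragmatic, non-inferiority, parallel-arm randomized controlled trial including 280 patients". Under Hypothesis, aim, and objectives {8 +12}, the hypothesis is that expiratory techniques "are non-inferior to tracheal suction in obtaining sputum samples from the lower respiratory tract". Study design and setting {9} and Sample size consideration {11} repeat the non-inferiority label.

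The parts that govern the analysis read differently:

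- The first objective asks: "Is the proportion of suitable (good quality) sputum samples different when comparing samples obtained by tracheal suction" (and by expiratory techniques).
- Definition of analyses population {20} says the primary analysis compares the two groups "to identify the most effective method for obtaining good quality sputum samples".
- Confidence interval and p-value {16+17+18} says that for the main analysis "95% confidence intervals will be reported", and that a p-value "less than 0.05 will be considered statistically significant". No limit is compared with any bound, and sidedness is not given.
- For the primary outcome, "a hierarchical mixed effect logistic model with and without imputed values will be utilized". Table 2 reports an odds ratio with its interval and P, with tracheal suction as the reference.
- Under the adjustments made after study start, a new power calculation is described in which "the clinical significant absolute difference was set at 15% points". That figure is not named a margin and is not mentioned again.

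**The concern.** A non-inferiority conclusion needs three things fixed in advance: a margin, the scale it is on, and a rule that the confidence limit must lie on the right side of it. The SAP supplies none of them as such. What it supplies is the apparatus for a test of difference.

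The risk is in how the result is read. If the odds ratio is not significant, a reader who holds only the stated hypothesis and the p-value criterion may take this as non-inferiority shown. Failure to detect a difference does not show that a deficit of a given size has been excluded. If instead a margin is chosen once the interval is known, that is the data-driven analysis the SAP says it exists to prevent.

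**Working it through.** **Inputs.** From Sample size consideration {11}: good quality in 90% of obtained samples with suction and 75% with expiratory techniques; no sample from 10% with suction; 260 patients; power 84% by Monte Carlo with logistic regression. Allocation is 1:1 (Randomization {10}), so 130 per arm. The 30% without a sample after induction can be read in two ways: 30% of the whole expiratory arm, or 30% of the half who failed the first technique (0.5 × 0.3 = 15% of the arm). Both are carried. Samples analysed are therefore 117 with suction, against 130 × 0.85 = 110.5 or 130 × 0.70 = 91 with expiratory techniques.

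**1. Reproducing the 84% as a test of difference (two-sided 0.05).** Power = Φ[(0.15 − 1.96 × SE₀)/SE₁], with SE₀ pooled and SE₁ unpooled.

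- 117 against 110.5: pooled rate 0.8271, SE₀ = 0.0502, SE₁ = √(0.09/117 + 0.1875/110.5) = 0.0497. Φ[(0.15 − 0.0983)/0.0497] = Φ(1.04) = 85.1%.
- 117 against 91: pooled rate 0.8344, SE₀ = 0.0520, SE₁ = √(0.09/117 + 0.1875/91) = 0.0532. Φ[(0.15 − 0.1018)/0.0532] = Φ(0.905) = 81.7%.

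A simulation of the Wald test on the log odds ratio (200,000 trials) gives 85.6% and 82.0%. The two readings bracket 84%.

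**2. The same inputs as a non-inferiority test with a 15-point margin (one-sided 0.025).** Power = Φ[(margin − assumed deficit)/SE₁ − 1.96] = Φ[(0.15 − 0.15)/SE₁ − 1.96] = Φ(−1.96) = 2.5%. Simulation gives 2.8–3.1%. The assumed deficit equals the margin, so no sample size raises this. At these rates the margin would have to be about 30 points for power near the stated figure (81–86%).

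**3. What a non-significant p would mean.** Simulation with 260 patients and 200,000 trials. Each range covers 15% and 30% uncollected in the expiratory arm.

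| True rates | p > 0.05 | 95% CI excludes a 15-point deficit | p > 0.05 and 15 points not excluded |
|---|---|---|---|
| 90% v 75% (SAP) | 14–18% | about 3% | 12–15% |
| 90% v 80% (assumed) | 44–48% | 19–20% | 25–29% |

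In the second row, 24.7/44.3 = 56% and 29.3/47.8 = 61% of the non-significant trials leave a 15-point deficit open.

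**4. Scale.** From 90%, a 15-point deficit is an odds ratio of (0.75/0.25)/(0.90/0.10) = 0.33. From an assumed 80% it is (0.65/0.35)/(0.80/0.20) = 0.46. The odds ratio that matches 15 points depends on the suction rate.

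**Limits.** The simulation has no random effects for personnel or site, because the SAP gives no variances for them. The abstract's 280 patients would give 84.4–87.6% in step 1 and leave step 2 unchanged.

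**The case against.** The best defence is that the pieces of a rule are present. The SAP commits to 95% intervals for the main analysis and gives a 15-point absolute difference, set by personnel who did not know the participants' outcomes. The p-value sentence is general and covers all analyses, and nowhere does the SAP equate p > 0.05 with non-inferiority. With the assumed 90% suction rate, 15 points also translates to an odds ratio of 0.33.

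This limits the point but does not remove it. A reader might infer that the trial cannot support a non-inferiority conclusion at all. The documents do not support that, because the planned interval could be held against a margin. What is missing is the link: no sentence names the margin or says that a limit must exclude it.

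Two other readings go too far:

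- **The 15 points are the intended margin and only need writing in.** Sample size consideration {11} assumes a true deficit of exactly that size, so the rule would succeed in about 3% of trials under the SAP's own rates. The figure fits the role of a detectable difference.
- **A significant deficit might still lie inside 15 points and mislead.** This is possible in principle, but at this sample size it occurred in at most about 0.2% of simulated trials.

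**Conclusion.** The point stands: the label is non-inferiority, while the objective, the decision criterion and the power calculation belong to a test of difference. This is more than detail left to a fuller document, because the SAP does state a criterion and that criterion does not address the hypothesis.

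The firmest evidence is the 84%. It matches power to detect a 15-point difference (about 82–86%) and does not match non-inferiority with a 15-point margin (about 3%). Both results use the SAP's own rates and the two readings of its missing-sample figure. The misreading risk of 44–48% against about 19% rests on an assumed truth of 90% against 80%, which is not in the SAP.

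The low power in step 2 does not show that the trial is too small for non-inferiority. If the true rates were equal at 90%, also an assumption outside the SAP, a 15-point margin would have about 94–96% power. The restated power therefore depends on the margin and rates the sponsor can justify.

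**What to change.** Before the data are analysed:

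1. In Confidence interval and p-value {16+17+18} and Analysis for primary outcome, state a justified margin, its scale and the confidence level, and say that non-inferiority is concluded only if the confidence limit excludes the margin. The value is for the sponsor to justify; none is proposed here.
2. Name which analysis decides, imputed or complete case.
3. If the margin is absolute, obtain the risk difference from the planned logistic model, saying how the random effects are handled and how results are pooled over imputations.
4. State that p > 0.05 is not evidence of non-inferiority.
5. Bring the first objective and the statement of purpose of the primary analysis into line with the hypothesis.
6. In Sample size consideration {11}, say that 84% is power to detect a difference, and give the power for the non-inferiority test with its assumed rates.

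If no margin can be justified, describe the trial as a test of difference and drop the non-inferiority conclusion.

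The cost is wording, a margin justification, a repeated power calculation and a small amount of extra analysis. No new data are needed. The restated power may be less favourable than 84%.
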